### Data Collection Tools

BP will be measured using validated electronic arm-cuff devices following standardized procedures: 3 measurements at 1- to 2-minute intervals after 5 minutes of rest, recording systolic and diastolic pressure in both arms following the European Society of Hypertension guidelines. Mediators document results immediately on structured forms and provide participants with referral slips if indicated. Sociodemographic, anthropometric, and medical history data will be collected using a paper-based questionnaire estimated to require 30 minutes per participant. The questionnaire included demographic data (age, sex, country of birth, languages spoken, and duration of residence), medical history (previous hypertension diagnosis, current medications, and cardiovascular events), health care access (insurance status, usual source of care, and barriers to access), and lifestyle factors (smoking, alcohol consumption, physical activity, and dietary habits). For participants with suspected hypertension, a standardized 3-month phone follow-up will be performed using a semistructured script to capture referral completion and treatment adherence. Administrative data on hospitalizations, diagnoses, and prescriptions will be accessed from the regional PMSI [32] and national health insurance databases. PMSI is a French hospital discharge database that compiles standardized clinical and administrative information on all inpatient stays in both public and private hospitals. It includes data such as patient demographics, diagnoses, medical procedures, and length of hospital stay. This system enables the construction of patient cohorts based on variables such as age, sex, comorbidities, and disease severity. Data are routinely collected from health care facilities, ensuring comprehensive population coverage and minimizing selection bias. Its use is governed by strict ethical and data protection regulations. No biological samples will be collected.

### Data Quality and Monitoring Procedures

Data collection forms are reviewed daily by team supervisors for completeness and consistency. Electronic data entry into the Ennov Clinical database is performed by trained research assistants with automatic range and consistency checks. There is regular verification of different aspects, including the appropriate completion of nonopposition documentation; the accuracy of transcription from paper forms to the electronic database; proper storage of source documents; adherence to protocol procedures; and finally, verification of a random sample of 10% of participant records against database entries.

### Safety Assessment

The intervention carries minimal risk. All procedures, including BP measurement and health interviews, are noninvasive and in line with routine prevention practices. No pharmacological treatments, invasive diagnostics, or biological sample collection are involved. Adverse events are not expected; however, participants experiencing persistently dangerously elevated BP (eg, >180/110 mm Hg) will be referred immediately for urgent care. No data safety monitoring board (DSMB) has been implemented because of the low-risk classification (category 3) of the intervention.

### Statistical Analysis

Statistical analyses will be conducted using Stata (version 19; StataCorp). Continuous variables will be described using means and SDs when normally distributed; for skewed distributions, medians and IQR will be reported. Normality will be assessed using visual inspection of histograms and quantile-quantile plots and confirmed with the Shapiro-Wilk test.

Comparisons of continuous variables between groups (eg, before vs after the intervention and intervention vs control regions) will be performed using the Student *t* test or the Mann-Whitney *U* test, as appropriate. The Student *t* test is a statistical method used to determine whether the means of 2 independent groups are significantly different from each other. It assumes that the data in each group are approximately normally distributed and that the variances are equal or similar.

Categorical variables will be summarized as absolute frequencies and percentages. Between-group comparisons will be conducted using chi-square tests or Fisher exact tests.

All statistical comparisons will be 2-sided, and results will be considered statistically significant if *P*<.05. Corresponding 95% CIs will be reported for all estimated parameters.

The primary outcome analysis will assess the difference in stroke incidence before and after the 2-year intervention period among residents of precarious neighborhoods within the CACL of French Guiana. Stroke incidence, derived from PMSI hospitalization data, will be compared across the 2 periods using the chi-square test. To evaluate temporal trends and detect structural breaks attributable to the intervention, segmented regression of interrupted time series (ITS) [33] data will be applied. The ITS model will estimate the immediate change in level and the change in slope after the intervention, while adjusting for autocorrelation and seasonality as necessary based on model diagnostics (Figure 3).

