## Results

This study was funded in 2022 and registered on ClinicalTrials.gov in April 2023 (NCT05814068). Recruitment for this study began in September 2023 and concluded on September 4, 2025, marking the end of the 24-month intervention period. During this period, 23,289 participants benefited from the intervention (ie, received at least 1 BP measurement and health education session), including 10,901 (46.8%) who completed the full enrollment questionnaire. Three-month telephone follow-up for participants with elevated BP was conducted as scheduled and completed by December 2025. Case report form (CRF) data entry and quality monitoring procedures were in progress as of February 2026, with database lock planned for March 2026 and primary outcome analysis expected between April 2026 and May 2026.

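### Unpaired continuous comparisons rest on a Shapiro-Wilk check and a Student t test; a Welch default without the check would be safer for before-v-after hospital records and costs almost nothing

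*Protocol article*

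**What the plan says.** All of this is in the Statistical Analysis section of the protocol article, except where noted.

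- Shape is judged from plots, then tested: "Normality will be assessed using visual inspection of histograms and quantile-quantile plots and confirmed with the Shapiro-Wilk test". Means and SDs are reported for normal variables, medians and IQRs for skewed ones.
- The contrasts are unpaired: "Comparisons of continuous variables between groups (eg, before vs after the intervention and intervention vs control regions" are the examples given. They "will be performed using the Student *t* test or the Mann-Whitney *U* test, as appropriate".
- The t test is explained as assuming that "the data in each group are approximately normally distributed and that the variances are equal or similar". No unequal-variance version is named.
- The comparisons are inferential: "All statistical comparisons will be 2-sided, and results will be considered statistically significant if *P*<.05". Intervals are promised too: "Corresponding 95% CIs will be reported for all estimated parameters".
- On size, the Results section reports 23,289 people reached, "including 10,901 (46.8%) who completed the full enrollment questionnaire". The sample size text, also under Statistical Analysis, gives about 238 strokes a year in precarious patients before the intervention and about 167 a year after it. It counts 60 monthly points before and 24 after.

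**The concern.** A normality test answers a question that sample size largely settles. In large files it flags departures too small to affect inference on means. In small files, where shape could matter, it has little power. Making it the confirming step lets sample size influence whether a variable is summarised by a mean or by a median, and whether the comparison targets means or ranks.

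The test that follows matters as well. The before-v-after contrast sets five years against two, so the groups are unequal. That is the setting in which the pooled-variance t test misses its nominal level when the spreads differ. The rank test does not repair this, because with unequal spread or shape it does not test a difference in means. At stake are the 5% level and 95% coverage that the section attaches to these secondary descriptive comparisons.

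**Working it through.** The article gives no figure of its own for this rule, so there is none to reproduce.

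**Inputs from the article.** Questionnaires: 10,901. Baseline stroke stays: 238 × 5 = 1,190, taking the annual figure as constant. Postintervention stays under the planned 30% reduction: 238 × 0.7 × 2 ≈ 333. Monthly points: 60 and 24, with autocorrelation 0.3 to 0.5. Two-sided alpha: 0.05.

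**Assumptions, because the article gives no values.** Gamma data with skewness 0.2 to 0.5, and a ratio r of the SD after to the SD before from 1/1.5 to 1.5.

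**Step 1: how often Shapiro-Wilk rejects at P<.05 (simulation).**

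| n | skewness 0.2 | 0.3 | 0.5 |
|---|---|---|---|
| 24 | 6% | 8% | 12% |
| 60 | 9% | 14% | 27% |
| 333 | 23% | 46% | 92% |
| 1,190 | 70% | 97% | 100% |
| 5,000 | 100% | 100% | 100% |

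At n=10,901 rejection is also 100% for all three values. Rounding alone is enough: exactly normal values recorded in steps of 0.1 SD are rejected 100% of the time at that size.

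**Step 2: level of the Student t test when means are equal.** Let the earlier group have size n₁ and variance 1, and the later group size n₂ and variance r².

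- Variance the test assumes: A = [(n₁ + n₂r²)/(n₁ + n₂)] × (1/n₁ + 1/n₂)
- True variance of the mean difference: T = 1/n₁ + r²/n₂
- Large-sample type I error: 2 × [1 − Φ(1.96 × √(A/T))]

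Example with n₁:n₂ = 5:2 and r = 1.5:

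- A = (5 + 2 × 2.25)/7 × (0.2 + 0.5) = 0.950
- T = 0.2 + 2.25 × 0.5 = 1.325
- √(0.950/1.325) = 0.847, and 1.96 × 0.847 = 1.66, so the error is 9.7%.

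| r (after/before) | 5:2 | 1,190 v 333 |
|---|---|---|
| 1/1.5 | 2.1% | 1.5% |
| 1/1.2 | 3.4% | 3.0% |
| 1 | 5.0% | 5.0% |
| 1.2 | 7.0% | 7.7% |
| 1.5 | 9.7% | 11.6% |

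Simulation with normal data at 1,190 v 333 agrees: 1.6%, 3.2%, 4.6%, 7.7% and 11.7% for Student, against 4.4% to 5.5% for Welch. At 42 v 42, Student stays between 4.7% and 5.3% for SD ratios from 0.5 to 2, so the imbalance drives the error.

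**Step 3: the rank test with equal means.** At 1,190 v 333 with skewness 0.5, Mann-Whitney rejects 9.3%, 4.8% and 15.4% at r = 1/1.5, 1 and 1.5. Welch rejects 5.6%, 4.8% and 4.4%. The excess is not an error against the rank test's own null, because unequal spread combined with skewness makes that null false. It shows that the test is not answering a question about means.

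**Step 4: monthly values.** Comparing 60 with 24 autocorrelated points as if independent gives the following type I errors:

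| Autocorrelation | Student | Welch | Mann-Whitney |
|---|---|---|---|
| 0.3 | 15.2% | 15.2% | 14.5% |
| 0.5 | 25.4% | 25.7% | 24.5% |

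No choice among the three tests repairs that use.

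**The case against.** Much of the case on the other side stands.

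- **No named outcome depends on this rule.** Stroke is analysed by interrupted time series with chi-square as a sensitivity check. The other event outcomes and prescription volumes also use interrupted time series, and repeated questionnaire measures use paired tests. A reader might infer that the primary result is at risk; the document does not support that.
- **The questionnaires have no before period.** They were collected during the intervention, so the 5:2 split cannot apply to them. A reader might infer that blood pressure and body measurements will be compared before v after by a faulty test. The hospital data are described as holding demographics, diagnoses, procedures and length of stay, so no such contrast is available. Large n and the unequal split coincide only in record-level hospital variables such as age or length of stay.
- **The check is not a mechanical gate.** Plots come first and the test is chosen as appropriate, so it does not follow that almost every variable must move to ranks. Even so, the section does not say which prevails when the plots look acceptable and the test rejects.
- **Wrong error rates need unequal spread.** The equal-variance remark explains the t test; it is not a commitment to use that test whatever the data show. With equal SDs, both tests hold about 5%.
- **The promised intervals are not contradicted.** A rank-based shift estimate can carry a 95% CI. The narrower point is that the effect measure would depend on the normality check.

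The remaining objection is that the t-test variant is a detail for an analysis plan. It carries less weight here because the article itself fixes the confirming test, names the two tests and declares the comparisons inferential.

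**Conclusion.** The point holds as a small improvement. Shapiro-Wilk is uninformative as a confirming step at the size of the questionnaire or stay-level data, and weak at the size of the monthly series. For before-v-after comparisons of hospital records, the Student test may run at about 7% to 12% if the smaller, later group is 1.2 to 1.5 times as variable. It may run at about 2% if the earlier group is 1.5 times as variable. Welch stays near 5% in every independent-data setting tried.

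These figures rest on assumed SD ratios and skewness and on a constant 238 strokes a year. A reader might conclude that the stated 5% and 95% are wrong; the document allows only that they may be. The consequence is confined to descriptive and incidental comparisons, and no conclusion about stroke or the other events changes.

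**What to change.** In the Statistical Analysis section:

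1. Remove Shapiro-Wilk as the confirming step and judge shape from the plots already planned.
2. Report both mean (SD) and median (IQR) for continuous variables.
3. Make the Welch mean difference with its 95% CI the default for unpaired comparisons of independent records. Use a log transform or a bootstrap CI where the plots show plain skewness, and keep the rank test as supplementary.
4. State that monthly values are not compared with any of these tests and belong in the interrupted time series model.

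The cost is a few sentences and one software option. Little is lost when variances are equal: with equal SDs, Welch and Student reject at practically the same rate at these sizes. Because the Results section places the primary outcome analysis in April to May 2026, the change should be dated, with a statement of whether these comparisons had already been run.

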### Randomization and Blinding

Because this study is nonrandomized and uses a quasi-experimental design, no randomization procedures will be used. Participants will be naturally exposed to the intervention as a function of their geographic residence. To limit assessment bias, the primary outcomes will be based on objective administrative data from hospital discharge records and national health insurance datasets. These datasets are not influenced by participants’ awareness of their inclusion in the study.

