## Discussion

### Principal Anticipated Findings

This community-based hypertension screening intervention in French Guiana’s precarious neighborhoods is anticipated to demonstrate a significant reduction in stroke incidence among socioeconomically vulnerable populations. On the basis of the comprehensive deployment of trained health mediators who screened >23,000 participants across 32 neighborhoods, we expect to observe a 20% to 30% reduction in stroke incidence in the 2-year postintervention period compared to the 5-year baseline period. If confirmed, this would represent one of the largest quasi-experimental demonstrations of stroke prevention through community-based hypertension screening in a low- to middle-income setting in Amazonia. It is anticipated that the intervention will also result in a significant decline in other cardiovascular and renal events compared to the preintervention period.

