However, several limitations must be acknowledged. The quasi-experimental design without randomization means that temporal confounders (such as concurrent public health campaigns, changes in health care access, or secular trends in treatment patterns) may influence outcomes independently of the intervention. Although we will attempt to control for these through comparison with nonintervention regions in French Guiana, unmeasured confounding remains possible. Reliance on administrative datasets, while ensuring comprehensive capture, may be subject to coding inaccuracies or changes in diagnostic practices over time. However, the use of validated *International Statistical Classification of Diseases and Related Health Problems, 10th revision* (ICD-10) codes for stroke diagnosis and the consistency of PMSI reporting requirements over the study period minimize this concern. Implementation heterogeneity across neighborhoods (varying in size, accessibility, and population composition) may introduce variability in intervention dose and reach. We will document coverage rates by neighborhood and explore heterogeneity in subgroup analyses, but differences in how intensively the intervention was implemented across neighborhoods may influence the results. For secondary outcomes assessed through participant questionnaires and telephone follow-up (eg, referral adherence, treatment initiation, and satisfaction), self-reported data may be subject to social desirability and recall biases. Additionally, loss to follow-up during the 3-month telephone interviews may affect internal validity for these secondary end points, although we plan to use multiple imputation techniques and will report sensitivity analyses restricted to complete cases. These limitations, however, do not affect the primary outcome analysis, which relies exclusively on objective administrative data. Finally, the exclusion of individuals under legal protection (eg, guardianship) is required by French research regulations but may reduce generalizability to populations with severe cognitive impairment or psychiatric conditions, groups that may also experience an elevated risk of cardiovascular disease. Despite these limitations, this study addresses a critical gap in stroke prevention research in underserved populations and will provide valuable evidence on the effectiveness and scalability of community-based hypertension screening in resource-limited settings.

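### The tests and confidence intervals named for individual participant data assume independent people or pairs, although participants were recruited neighborhood by neighborhood, so some intervals are likely too narrow.

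*Protocol article*

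**What the plan says.** The methods for individual data are in the Protocol article, Statistical Analysis.

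- **General rules.** Continuous variables are compared between groups with Student t or Mann-Whitney tests. For categorical variables, "Between-group comparisons will be conducted using chi-square tests or Fisher exact tests". On precision, "Corresponding 95% CIs will be reported for all estimated parameters".
- **Questionnaire data.** For repeated measures on participants, the section names McNemar or Wilcoxon signed-rank tests.
- **Dependence addressed.** Two kinds are covered: pairing within a person (McNemar) and autocorrelation in the interrupted time series (ITS). Nothing is said about correlation between people from the same neighborhood.

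Recruitment is described by area.

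- Randomization and Blinding: "Participants will be naturally exposed to the intervention as a function of their geographic residence".
- Intervention or Treatment: teams spend one or two days in a neighborhood per visit, working from fixed posts and door to door.
- Principal Anticipated Findings: mediators "screened >23,000 participants across 32 neighborhoods".
- Results: "23,289 participants benefited from the intervention", "including 10,901 (46.8%) who completed the full enrollment questionnaire".
- Strengths and Limitations: "Implementation heterogeneity across neighborhoods (varying in size, accessibility, and population composition) may introduce variability in intervention dose and reach". The planned response is to report coverage by neighborhood and explore subgroups; no change to the variance is mentioned.
- Study Design and Setting: the 3-month telephone call goes only to participants with elevated blood pressure. Their number is not given.

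**The concern.** People reached at the same post, in the same household or during the same visit tend to resemble one another. They share housing, access to care, language, and the mediators who screened and questioned them. Every test named for individual data treats people, or pairs, as independent. McNemar does not remove the problem: it deals with the two measurements on one person, but still assumes that different people's changes are unrelated.

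Screening yield, referral adherence, satisfaction and treatment uptake are secondary endpoints, and Comparison to Prior Work says they should inform policy and scale-up. If the named methods are applied as written, the precision reported for some of them will be overstated.

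**Working it through.** The article gives no precision, ICC or design effect for participant-level outcomes, so there is no figure of its own to reproduce. Its percentage checks: 10,901 / 23,289 = 46.8%.

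**Inputs**
- Enrolled with questionnaire: 10,901 (Results).
- Neighborhoods: 32 (Principal Anticipated Findings). This count is stated for everyone screened; I assume all 32 contributed enrolled participants.
- ICC 0.005 to 0.02: assumed.
- Share of enrolled participants with elevated blood pressure and 3-month data: 30%, assumed.
- Discordant pairs for McNemar: 20%, assumed, with direction of change clustered at the same ICC.

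**Formulas**, with m the mean number per neighborhood
- Design effect: DE = 1 + (m − 1) × ICC
- Interval widening: √DE
- True error of a nominal 5% two-sided test: 2 × (1 − Φ(1.96/√DE))

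**1. Overall proportion, all enrolled.** m = 10,901 / 32 = 340.7. The independent-data half-width for a proportion of 50% is 1.96 × √(0.25/10,901) = 0.94 percentage points.

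| ICC | DE | Widening | Effective n | Half-width, points |
|---|---|---|---|---|
| 0.005 | 1 + 339.7 × 0.005 = 2.70 | 1.64 | 4,040 | 1.54 |
| 0.01 | 4.40 | 2.10 | 2,479 | 1.97 |
| 0.02 | 7.79 | 2.79 | 1,399 | 2.62 |

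At an ICC of only 0.001, DE is 1.34 and the widening 1.16. Unequal neighborhood sizes make it worse. With an assumed coefficient of variation of 0.8, DE = 1 + (1.64 × 340.7 − 1) × ICC = 3.79, 6.58 and 12.15 for the three tabled ICCs.

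**2. Proportion in the elevated-pressure subset.** 0.30 × 10,901 = 3,270, so m = 102.2. DE = 1.51, 2.01 and 3.02; widening 1.23, 1.42 and 1.74. If the share is 20%, DE runs from 1.34 to 2.34; if 50%, from 1.85 to 4.39.

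**3. McNemar in that subset.** Only discordant pairs carry information: 0.20 × 102.2 = 20.4 per neighborhood. DE = 1 + 19.4 × ICC = 1.10, 1.19 and 1.39. The true error is 6.1%, 7.3% and 9.6%.

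**4. Where there is no inflation.** In a simulation with 32 neighborhoods of 341 and 4,000 replicates, a chi-square test between groups mixed evenly within every neighborhood rejected in 4.5 to 5.3% of replicates at every ICC tried (0.001 to 0.05).

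**The case against.** **The analysis plan is not shown.** The article says participant-level analyses will include paired tests, which is not exhaustive, and the Abstract mentions regression models without giving their form. A clustered variance could be specified elsewhere. That lowers certainty, but the published text does assign specific tests to these data, and none of them allows for clustering.

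**All precarious neighborhoods are targeted.** If inference stops at these neighborhoods, they act more like strata than a sample of clusters, and the full multiplier does not follow. This limits the size of the effect. It does not remove it: people reached at one post, visit or household remain correlated, and the study wants conclusions that extend beyond these neighborhoods.

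**A reader might infer a false-positive rate of 23 to 48%.** The error formula gives that range for DE 2.7 to 7.8, and simulation agrees (23.2 to 47.6%), but only for a chi-square comparison between sets of whole neighborhoods. The documents do not clearly plan such a test on questionnaire data. The between-group examples in Statistical Analysis are before versus after and intervention versus control regions, and no questionnaire is described in control regions. Nor does this rate apply to asking whether the neighborhoods differ at all, because under that null hypothesis there is no variation between them.

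**A reader might apply 10,901 to every participant-level outcome.** The documents do not support that, since referral completion and treatment initiation are captured at a call made only to part of the sample.

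**A reader might take the limitations paragraph as expecting outcomes to differ by neighborhood.** It speaks of variation in dose and reach, and says this may influence results; it does not say that satisfaction or adherence will vary.

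**Conclusion.** The point stands in limited form. As written, the named methods are likely to give intervals that are too narrow for overall participant-level proportions and for any neighborhood-level contrast. Over the assumed ICC range, the understatement is a factor of 1.6 to 2.8 for outcomes measured in all enrolled participants, and 1.2 to 1.7 for 3-month proportions under the 30% assumption. The plain McNemar test is mildly anticonservative in that subset.

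In absolute terms the corrected half-width for an overall proportion remains below 3 percentage points with equal-sized neighborhoods, so this is a matter of honest precision, not of lost information.

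It would go too far to say that every participant-level result is compromised. Contrasts between groups mixed within neighborhoods are unaffected. So are the primary stroke outcome and the ITS analyses, which use aggregated administrative data. The ICC, the subset share, the discordance and the spread of enrolled participants over all 32 neighborhoods are assumptions. The change should be made, but nothing in the main conclusion depends on it.

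**What to change.** Amend Statistical Analysis in two places.

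1. State that participant-level estimates, confidence intervals and regressions use neighborhood as the cluster. Either use cluster-robust variance with a small-sample reference (t on about 31 degrees of freedom, that is 32 − 1), or a mixed or GEE model with neighborhood as the cluster. A Rao-Scott adjusted chi-square can replace the plain test for categorical comparisons.
2. Replace the plain McNemar test with a cluster-adjusted version.

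When reporting, give the number of neighborhoods that contributed to each outcome and the estimated ICC, so that the assumed range above can be checked.

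No new data are needed if neighborhood is recorded for each participant, and clustered variance is a single option in standard software. The cost is wider intervals and some loss of nominal significance.
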